#### 3.1.3. Qualitative Analysis

During the semi-structured follow-up interviews, the interviewer will write down each word expressed by the participant. Most participants are rather short of words and need time to formulate their experiences. Each word in the written material is read out loud for the participant at the end of the interview to ensure the participant agrees to what is reported and that they accept the text. This procedure replaces member checking with this population, as audio recording mostly has a disturbing effect, and as they might have difficulties in remembering what they expressed, having a written text for several weeks later is very helpful. The texts will be analyzed through phenomenological analysis and will add to the results in the form of short theme-based narratives on developments in work situation, social and relational issues and patient reported overall experiences of participation in the study. Additionally, music improvisation analysis will add to the results concerning progression in levels of contact in the musical interplay of the therapeutic relationship.

## 4. Discussion

### 4.1. Blinded Design as an Innovation

This study is the first study in music therapy in patients diagnosed with schizophrenia using a randomized, controlled and blinded design. There are numerous studies and Cochrane reviews showing the positive results of music therapy on global functioning, including negative symptoms in patients diagnosed with schizophrenia where music therapy was added to standard care, comparing this to standard care alone [4,6,7].

This study will investigate if negative symptoms can be reduced when participants are offered music therapy performed by a professional music therapist, as compared to an active comparator where music listening to selected playlists is performed by a non-music therapist. The design adjusts for the Hawthorne effect, which may positively bias results of an intervention when only comparing this to standard care. This study will only capture the immediate effect on negative symptoms (if any) of the intervention. A four week follow-up includes solely a qualitative interview (see Section 2.4.6), where the subjective experiences of the participants can be unfolded. The timespan for this follow-up is rather short and could be claimed as a limitation of the study. As mentioned above, the four weeks timespan was chosen as the participants most commonly are chronically ill and cognitive deficits could result in recall bias.

#### 4.1.1. Challenging in Blinding

We are aware that the blinding of participants, as performed in this study, cannot be compared to a placebo blinding, as the intervention is a face to face procedure, and the therapists performing the interventions are not blinded.

#### 4.1.2. Challenges of the Design

We are also aware that applying a design as close to a biomedical design as possible, in an examination of a population with a complex disease and with low motivation for participation, is ambitious. We are prepared for challenges. We plan to cooperate with relevant staff members and relatives concerning motivation, attendance and other experienced challenges by the participants.

## 5. Conclusions

### Reduction in Sample Size Due to Challenges

The trial status is currently ongoing. Recruitment started in March 2016 and will continue until the end of May 2019, with the expected last participant visit in December 2019. Due to low rates of recruitment, a total of 47 participants have been included by November 2018, from the 177 referred to the study (see Figure 1). We currently aim to include a total of 60 participants. Concerning blinding, we have currently been informed that three participants receiving intervention II have expressed that they know they are not receiving music therapy due to previous experiences with music therapy. So they are not blinded. This will be transparent in the analysis of the data. In spite of challenges concerning motivation and attendance, many participants have so far been able to attend all sessions offered. The results of the current trial will be widely disseminated at national and international scientific conferences and in further scientific articles.

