## Abstract

**Background:** Three Cochrane reviews show that music therapy has a positive effect on schizophrenia concerning general functioning and positive/negative symptoms. This study aims to replicate these results in the Danish health system, a requirement for recommendation in guidelines from the Danish National Board of Health. **Methods:** The study is a randomized, controlled multi-site study, with a blinded design, aiming to include 90 participants who are 18–65 years in age, diagnosed according to ICD-10 with a schizophrenia diagnosis. The participants are randomized to one of two different music therapy activities for 25 weekly sessions. The study interventions are added to standard care. Outcome measures are rated at baseline, after 15 sessions and post therapy. A qualitative interview is performed as a one month follow up at the end of study. The primary intended outcome is a reduction in negative symptoms. The secondary intended outcome is progression in quality of life, alliance and psychosocial functioning. **Results:** As this study is still running, the results are not yet available. **Conclusion:** The study will investigate the direct effects of music therapy on negative symptoms as part of schizophrenia in a blinded, randomized trial. If proven effective, music therapy can be added to the small treatment armamentarium of effective therapies for negative symptoms in patients with schizophrenia.

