### 2.7. Sample Size

#### Estimation of Sample Size

Utilizing previous data, we estimated an effect size of 0.6 (medium effect according to Cohen’s d). With a selected level of significance of 0.05 and a power of 0.8, a power calculation performed in R with a conservative approach (applying a two-sided *t*-test with two samples), resulted in each group having to count a minimum of 44.5 persons. The data utilized in the power calculation did not use an active comparator, which might result in a lower effect size in the current study. We furthermore estimate a drop-out of 10–20% of participants, resulting in an estimated required sample size of 60 persons in each group.

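### The original target is given as both 90 and 120, and power was not restated after the cut to 60 in total: 63% with no loss, 58–53% with the planned loss

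*Protocol article*

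**What the plan says.** Three totals stand in the current text of the protocol article.

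- **Abstract, Methods:** "with a blinded design, aiming to include 90 participants".
- **Section 2.7, Estimation of Sample Size:** the test is a two-sided two-sample t-test at alpha 0.05 with a target power of 0.8, and the effect assumed is given as "we estimated an effect size of 0.6 (medium effect according to Cohen’s d"). These inputs give a minimum of 44.5 per group. A drop-out of 10–20% is then added, "resulting in an estimated required sample size of 60 persons in each group", which is 120 in total.
- **Section 5, Reduction in Sample Size Due to Challenges:** low recruitment is given as the reason, 47 participants had been included by November 2018, and "We currently aim to include a total of 60 participants".

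Section 2.7 also carries a caveat on the effect size: "The data utilized in the power calculation did not use an active comparator", so the effect in this trial might be smaller. No smaller effect is worked through. Section 5 does not say which earlier target was reduced, and gives neither the power nor the detectable effect at 60.

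**The concern.** A reader of the abstract alone takes the trial to be aiming for 90. A reader of section 2.7 takes 120 as the requirement. A reader of section 5 learns that the target is 60, half the number that section 2.7 calls required. The figure 60 also appears twice with different meanings, per group in section 2.7 and in total in section 5, and the two are easily confused.

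The only power figure a reader meets is 0.8. If it is carried over to the current target, the trial looks better able to detect the planned effect than it is. That matters most if the primary result is not statistically significant. How much such a result says against an effect of 0.6 depends on the power at the size actually reached, which the article does not give.

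**Working it through.** **Inputs.** d = 0.6, two-sided alpha 0.05, power 0.80, two-sample t-test and drop-out 10–20% (all section 2.7). Totals of 90 (abstract), 120 (2 × 60, section 2.7) and 60 (section 5). Equal groups are implied by section 2.7; no allocation ratio is stated.

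**Method.** With n evaluable per arm, the t statistic has 2n − 2 degrees of freedom and noncentrality d·√(n/2). Power is the probability that it falls outside ± the 97.5% t quantile.

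**Step 1: reproduce the article's figure.** Solving for 80% power at d = 0.6 gives n = 44.59 per arm, in line with the stated 44.5. A one-sided test would need only 35.0, so the calculation was two-sided, as stated.

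**Step 2: the drop-out allowance.** 45/(1 − 0.10) = 50 and 45/(1 − 0.20) = 56.25, rounded up to 57 per arm. The stated 60 per arm corresponds to a loss of about 25%, since 45/0.75 = 60, and so lies slightly above the stated range. It is on the safe side.

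**Step 3: where 90 may come from.** 2 × 44.5 = 89, and 2 × 45 = 90. The abstract's figure therefore matches the number before any drop-out allowance. This is an inference; the article does not explain it.

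**Step 4: power at each total, d = 0.6.**

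| Total randomised | No loss (n per arm) | 10% loss | 20% loss |
|---|---|---|---|
| 120 | 0.90 (60) | 0.87 (54) | 0.83 (48) |
| 90 | 0.80 (45) | 0.76 (40.5) | 0.71 (36) |
| 60 | 0.63 (30) | 0.58 (27) | 0.53 (24) |

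For example, at 27 per arm the noncentrality is 0.6 × √13.5 = 2.20, against a critical value of 2.01 on 52 degrees of freedom, and the power is 0.58.

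**Step 5: effect detectable with 80% power at 60 in total.** d = 0.74 with no loss, 0.78 with 10% loss and 0.83 with 20% loss.

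**Step 6: if the active comparator shrinks the effect.** The article gives no smaller value, so these are assumptions. At 60 in total, with 0%, 10% and 20% loss, d = 0.5 gives power of 0.48, 0.44 and 0.40, and d = 0.4 gives 0.33, 0.30 and 0.27.

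**Step 7: what baseline adjustment might recover.** Let r be the correlation between the baseline and final PANSS negative scores; the article does not give it. If 0.6 is on the raw-score SD, adjustment raises the effective d to 0.6/√(1 − r²). If it is on the change-score SD, the effective d is 0.6·√(2/(1 + r)). At 27 per arm:

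- Assumed r = 0.5: effective d = 0.69 on either scale, power 0.70.
- Assumed r = 0.6: effective d = 0.75 and power 0.77 on the raw-score SD; effective d = 0.67 and power 0.68 on the change-score SD.

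Under these assumptions power stays below 0.80.

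**The case against.** **The reduction is disclosed.** Section 5 reports it under a heading that says so and gives the reason. A reader might infer that the article hides three conflicting targets. It does not: 60 is an open change of plan, and only 90 against 120 is unexplained. This objection stands.

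**The article never claims 80% power for 60 participants.** The 0.8 belongs to the original calculation, which is arithmetically right. The fault is a missing restatement, not a wrong sum. This also stands, but disclosing a smaller number does not disclose what it does to the power.

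**The 53–63% is not the power of the planned analysis.** Section 3.1.1 plans a mixed model for PANSS and an intention-to-treat analysis of all participants, with a final assessment at discontinuation where possible. Table 1 shows a PANSS rating after session 15. An unadjusted t-test that discards everyone who drops out is therefore pessimistic. This is fair, and the figures should be labelled as t-test power. The gain cannot be quantified from the article, and its own caveat on the comparator pulls the other way.

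**The word conservative.** A reader might take it to describe the choice of 0.6, and so call it misleading. Section 2.7 attaches it to the test: "a power calculation performed in R with a conservative approach (applying a two-sided" two-sample t-test. The word can stay.

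**The aim to replicate.** The abstract says "This study aims to replicate these results in the Danish health system", although the earlier studies compared music therapy with standard care alone. A reader might conclude that the trial misstates its comparison. The introduction, the hypothesis in section 1.2 and the discussion state the active-comparator comparison clearly. This is a separate, minor wording matter in the abstract and has no bearing on power.

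**How a null result will be read.** Nothing in the article says that a non-significant result would be taken as proof of no effect, so that remains a risk and not a stated intention.

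**Conclusion.** The point holds in a limited form. The abstract and section 2.7 disagree on the original target (90 against 120) without explanation, and the only stated power was not restated when the target fell to 60 in total. By the article's own t-test and inputs, 60 in total gives 63% power with no loss and 58–53% with 10–20% loss. At 120 in total with the same loss it would have been 87–83%. The effect detectable with 80% power moves from 0.6 to 0.74 with no loss, or 0.78–0.83 with loss.

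This rests on equal groups, on d = 0.6, and on participants who drop out contributing nothing. The planned mixed model relaxes the last assumption, so the power of the actual analysis may be somewhat higher. A smaller effect against the active comparator would make it lower. The article does not support the claims that 80% power is asserted for 60, that the original calculation is wrong, or that the reduction is concealed.

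**What to change.** 1. Keep the calculation in section 2.7 as the record of the original plan. Overwriting it would lose the basis of the design.
2. Make the abstract and section 2.7 agree on the original target. If 90 was the number before the drop-out allowance, say so.
3. Give 60 in total as the current target wherever a current target is stated, and keep it distinct from the original 60 per group.
4. Add after the reduction: *60 randomised with 10–20% loss gives 53–58% power for d = 0.6 by the same t-test; the effect detectable with 80% power is 0.78–0.83, so a non-significant result is not evidence of no effect.*
5. Adjust the planned mixed model for the baseline PANSS negative score, which is already collected. The analysis plan is not shown, so if this is already specified there, nothing more is needed. Do not quote a power gain unless a baseline–outcome correlation is stated as an assumption, together with the SD on which d = 0.6 is expressed.

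The cost is wording plus, at most, one model term. No extra patients or assessments are needed. The downside is that the stated power becomes less favourable.

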## Figures and Tables

**Figure 1 medicines-06-00046-f001:**
[figure not shown]
Flow diagram of the experiment design. As the recruitment process is currently running, only the inclusion data can be presented.

**Table 1 medicines-06-00046-t001:** A SPIRIT diagram on screening procedures.

	Screening	Baseline		After Fifth before Sixth Offered Session	After Fifteenth before Sixteenth Offered Session			Less Than Eight Days after the Last Session Termination ^1^			Follow up 4–5 Weeks after Termination
No of visit	1	2		3	4			5			6
Performed by ^2^			MT/T	RP	PN	MT	RP	PN	MT	RP	RP
Information and consent	x										
Demographical data ^3^	x										x
Status of medicine	x	x ^4^			x			x			
History of abuse	x	x ^4^			x			x			
History of music therapy ^5^	x	x ^4^									
Inclusion and Randomization		X									
PANSS	x	x ^6^			x			x			
Brief Negative Symptom Scale (BNSS)	x	x ^4^			x			x			
WHOQOL	x	x ^4^			x			x			
Calgary Depression Scale for Schizophrenia (CDSS)	x	x ^4^			x			x			
Udvalg for Kliniske Undersøgelser (UKU), otherwise Task Force for Clinical Investigations	x	x ^4^			x			x			
Global Assessment of Functioning (GAF)	x	x ^4^									
Helping Alliance Questionnaire (HAQ-II)				x			x			x	
MIRS Only experimental group I			x			x			x		
Start of weekly interventions, groups I and II			x								
Start McGlashan rating after each intervention for experimental group I			x								
Termination of weekly interventions for groups I and II									x		
Interview											x

^1^ Is not performed if screening procedure after fifteenth session but before sixteenth offered session is performed ≤14 days earlier. ^2^ PN = rroject nurses; MT = music therapists group I, therapist group II; RP = research participant. ^3^ Sex, age, ethnicity, level of education, social and work situation. ^4^ Is not performed if performed by screening ≤28 days earlier. ^5^ Music therapy and other formalized music related offers other than trial treatment are registered. ^6^ Is not performed if positive and negative syndrome scale (PANSS) in screening is performed ≤14 days earlier.
